### Data sources and data collection procedures

Data are available from three different sources: 1) the Needs Portal, 2) SACWIS archival data, and 3) EPIC survey data. Needs Portal data are used to track fidelity indicators in real benchmark dates over the course of implementation. SACWIS data are obtained quarterly from Ohio Department of Job and Family Services (ODJFS) via an encrypted password-protected USB drive. This is administrative data that are routinely collected as part of the investigative and intervention process resulting from a referral for a child abuse and neglect investigation. The final source of data are EPIC family surveys administered at the time of enrollment and again at 6 to 12 months following program completion. Parents complete the survey for themselves and for one focal child. Respondents receive a $25 gift card for completing each survey.

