**Methods:**

EPIC is a quasi-experimental study. Under the program**,** child welfare-involved adults who screen positive for substances are matched with a peer recovery supporter. Participants are also incentivized to participate in family treatment drug court, medications for opioid use disorders and home-based parenting supports. Participating adults (*N* = 250) are matched with comparison groups from counties participating in a separate intervention (Ohio START) and to those receiving treatment as usual, resulting in a final sample of 750 adults. Primary outcomes including addiction severity, child trauma symptoms, resilience, and attachment are assessed at baseline and at program completion. Additional outcomes include timely access to treatment services, length of placement in out-of-home care and recidivism into the child welfare system.

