## Methods / design

The overall goals and objectives of the intervention are:
Increase timely access to services among substances abusing parents involved in the child welfare system in Fairfield and Pickaway counties1.1 Develop procedures to coordinate services between the child welfare system, substance abuse and behavioral health providers, and juvenile/family court in a specified single MOU.1. 2 Conduct substance abuse and trauma-exposure screening and assessment within 30 days of entering the child welfare system.1. 3 Reduce the wait time between referral to services and initiation of substance use and behavioral health services.Enhance child safety and improve permanency2.1 Reduce length of stay in out-of-home placement for children in EPIC program compared to substance-affected families not receiving EPIC.2. 2 Increase rates of reunification among families involved in EPIC compared to substance-affected families not receiving EPIC.2. 3 Reduce recidivism for child welfare investigations and re-entries into foster care among parents receiving EPIC compared to substance-affected families not receiving EPIC.2.4 Identify which intervention components implemented via EPIC were more likely to increase positive outcomes for families.Increase child, parent, and caregiver well-being3.1 Decrease substance use/abuse addiction severity among parents and the percentage of parents completing substance abuse treatment who maintained abstinence post-treatment.3. 2 Reduce trauma symptoms experienced by children.3. 3 Increase resilience and attachment in children.3.4 Increase knowledge about trauma-exposure among kinship caregivers.3.5 Improve parenting among kinship caregivers.

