**Fig. 1 Fig1:**
[figure not shown]
Enhancing Permanency in Children and Families (EPIC): Case Flow. Parents complete the UNCOPE assessment within 7 days of substantiated report of child abuse or neglect. Parents receive a drug screen if they self-identify on the UNCOPE or a caseworker suspects substance use. Parents who screen positive are eligible for EPIC and are 1) linked to a peer recovery supporter, 2) referred to family treatment drug court, with the option of medications for opioid use disorders, and 3) receive in-home parenting based on the Nurturing Parenting Program. Participants work with assigned caseworkers to determine the most appropriate combination of services

To incentivize participation in FTDC, parents receive a $200 gift card upon completing their substance abuse assessment and an additional $200 retails gift card for every 3 months they remain involved with the court. Parents may consent to one or all three components of EPIC based on the specific needs of each family, however all parents receive intensive case management services, including frequent home visits from caseworkers and peer recovery supporters. All procedures involving human participants were approved by The Ohio State University’s Institutional Review Board (#2018B0001).

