### Outcome measures

All outcome measures are assessed at baseline and again at 6 months.

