### Statistical plan

Baseline descriptive statistics including sociodemographic characteristics, addiction severity and child welfare allegations will be provided for EPIC participants and comparison groups. For continues variables, means and SDs will be provided and for categorical variables, counts and percentages are provided.

Due to the likelihood of censored measures when families are still involved in the child welfare system, survival analysis will be utilized to assess program effects on length of stay in out of home care. Logistic regressions will be used to estimate the relationship between activities and family was reunification, subsequent child maltreatment investigations, and subsequent child maltreatment substantiations. A series of linear regressions will be used to estimate the relationship between our outcome measures and various independent variables (e.g., age, biological sex). Additionally, a paired samples t-test will be conducted to examine the changes in mean scores in child, parent and caregiver well-being outcomes (e.g. ASI or CBCL) between baseline and 6-months follow-up.

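### The follow-up survey is dated in three ways that no program length reconciles, and two of them run from a program completion that is not one common event across families

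*Protocol article*

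**What the plan says.** Four sections of the protocol article date the follow-up of the primary and well-being outcomes.

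- Abstract, Methods: "Primary outcomes including addiction severity, child trauma symptoms, resilience, and attachment are assessed at baseline and at program completion".
- Outcome measures: "All outcome measures are assessed at baseline and again at 6 months".
- Data sources and data collection procedures: "EPIC family surveys administered at the time of enrollment and again at 6 to 12 months following program completion".
- Statistical plan: the paired t-test on the well-being scales examines change "between baseline and 6-months follow-up".

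Two statements in the text around Fig. 1 show that the end of the program is not a fixed date. Court involvement has no stated length; parents receive "an additional $200 retails gift card for every 3 months they remain involved with the court". The content also differs by family: "Parents may consent to one or all three components of EPIC based on the specific needs of each family". Under Consent and withdrawal from study, parents may leave whenever they wish. The article does not define program completion, and it does not say when a parent who never completes is surveyed.

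The Power analysis section gives power 0.88 for the paired t-tests with N = 250, an effect size of 0.2 and a type I error of 0.05.

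**The concern.** The same outcomes cannot have been planned for all of these dates. Staff scheduling surveys from one section would call families at a different time from staff using another, and the before-after test would then pool visits many months apart. A missed or mistimed survey cannot be recovered later.

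The choice of anchor matters as well as the choice of month. A date counted from enrolment exists for every enrolled parent. A date counted from completion exists only for parents who complete, and for them it depends on how long they stayed and which components they took. In this population completion is plausibly related to addiction severity, which is a primary outcome. The paired t-test has no control group to absorb such selection, so a completion-anchored survey risks showing improvement that partly reflects who was left to be surveyed.

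**Working it through.** **1. Can the three dates agree?** Let L be the program length in months from enrolment. The article does not give L.

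| Section | Survey date, months from enrolment |
|---|---|
| Outcome measures; Statistical plan | 6 |
| Abstract, Methods | L |
| Data sources and data collection procedures | L + 6 to L + 12 |

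- The first and second rows agree only if L = 6.
- The third row reaches 6 only if L + 6 = 6, that is L = 0.
- The third row never equals the second, because L + 6 is greater than L for every L.

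So no L satisfies all three. Because L is unknown, the spread is shown for two assumed values. With L = 6 the dates are 6, 6, and 12 to 18 months. With L = 12 they are 6, 12, and 18 to 24 months.

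**2. Reproducing the stated power.** Inputs from Power analysis: effect size d = 0.2, n = 250, alpha = 0.05. Sidedness is not stated.

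For a paired t-test, power comes from the noncentral t distribution with n − 1 degrees of freedom and noncentrality d × √n. Here the degrees of freedom are 249 and the noncentrality is 0.2 × √250 = 3.16.

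- Two-sided: 0.883, which matches the stated 0.88.
- One-sided: 0.934, which does not match.

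The stated figure is therefore a two-sided test with a baseline and a follow-up value from all 250 EPIC parents. Power first reaches 0.88 at 248 pairs, so almost no loss is allowed for.

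**3. What follow-up in completers alone would do to power.** The completion rate is not in the article, so it is varied. The effect size is held at 0.2.

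| Assumed completion | Pairs | Power |
|---|---|---|
| 100% | 250 | 0.883 |
| 90% | 225 | 0.848 |
| 80% | 200 | 0.804 |
| 70% | 175 | 0.749 |
| 60% | 150 | 0.682 |
| 50% | 125 | 0.602 |

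Power stays at 0.80 or above with at least 199 pairs (199/250 = 79.6%).

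This table measures lost precision only. It does not measure selection. If completers improve more than the rest, the test could reject more often than the table suggests, and for the wrong reason. The article gives no figure from which to size that bias.

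**The case against.** The strongest reply is that the operative sections already agree. Outcome measures and the Statistical plan both say 6 months, and the power calculation uses the full EPIC sample of 250, which is the opposite of a completer-only analysis. On this view the abstract and the data-collection section are loosely worded. The latter might even mean 6 to 12 months after enrolment, once the program is over, which would put 6 months at the lower edge of its window.

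Part of this stands. The 6-month date has the best support in the text and is the natural one to keep. The softer reading is not what the sentence says, however. Even if it is adopted, a window of 6 to 12 months is not a 6-month visit, and the abstract's date fits only if completion happens to fall inside that window. Condensing a protocol into an article explains omissions, but not conflicting statements.

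A reader might infer several stronger things that the documents do not support:

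- *That only completers are measured.* No section excludes non-completers, and completion could mean case closure, which every family might reach.
- *That parents who do well are surveyed earlier.* Nothing says so. The court incentive pays for staying, so a parent who does well may stay longer.
- *That follow-up of comparison families is left undefined.* It is not clear that they are surveyed at follow-up at all. The paired t-test and linear regression are powered on 250, whereas the survival and logistic analyses are powered on 750. The Statistical plan mentions addiction severity in the comparison groups only at baseline.
- *That days in care and reunification are cut off at 6 months.* Outcome measures, read literally, covers them. But the Statistical plan chooses survival analysis because some families will still be in the system, and the administrative data arrive quarterly.
- *That objective 3.1 has the same flaw.* Its reference to "the percentage of parents completing substance abuse treatment who maintained abstinence post-treatment" concerns finishing substance abuse treatment, not the EPIC program, and it sets no survey date. Its denominator and its place after the verb for a decrease are separate matters of estimand and grammar.

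**Conclusion.** The point holds as an internal contradiction about when the survey-based primary and well-being outcomes are measured. Three dates are stated and no program length satisfies them all; this needs no outside assumption.

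The consequence is conditional. If the survey is run from program completion, it has no defined date for parents who withdraw or never complete and a variable date for the others, and the uncontrolled before-after test is then open to selection of the more successful parents. The plan does not state that it will do this, and bias toward benefit is a risk here, not an established result.

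The power of 0.88 is arithmetically correct. Its exposure depends on an unstated completion rate: if only completers were measured, power would run from about 0.85 at 90% completion to 0.60 at 50%, falling below 0.80 with fewer than 199 pairs. These figures assume the effect size stays at 0.2.

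**What to change.** Reconcile the abstract, Outcome measures, Data sources and data collection procedures, and the Statistical plan to one survey time.

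- Count it from enrolment and state a window around it. Six months is already the date in Outcome measures and the Statistical plan, and keeping it leaves the planned paired test unchanged.
- Apply it to every enrolled EPIC family, whether or not they complete any component.
- If comparison families are surveyed, use the same clock from their index date. If they are not, say so.
- Limit the 6-month sentence in Outcome measures to the survey outcomes, so that it does not conflict with the survival analysis of the administrative child welfare data.

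The cost is protocol wording and survey scheduling, plus the effort of tracing parents who leave the program. No additional survey is required.

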### Statistical plan

Baseline descriptive statistics including sociodemographic characteristics, addiction severity and child welfare allegations will be provided for EPIC participants and comparison groups. For continues variables, means and SDs will be provided and for categorical variables, counts and percentages are provided.

Due to the likelihood of censored measures when families are still involved in the child welfare system, survival analysis will be utilized to assess program effects on length of stay in out of home care. Logistic regressions will be used to estimate the relationship between activities and family was reunification, subsequent child maltreatment investigations, and subsequent child maltreatment substantiations. A series of linear regressions will be used to estimate the relationship between our outcome measures and various independent variables (e.g., age, biological sex). Additionally, a paired samples t-test will be conducted to examine the changes in mean scores in child, parent and caregiver well-being outcomes (e.g. ASI or CBCL) between baseline and 6-months follow-up.

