### Evaluation design

To evaluate EPIC, a quasi-experimental design will be employed through a two-stage sampling procedure. This design provides the ability to assess (1) the effects of EPIC on access to services for the families in the two intervention counties, and (2) the independent effects of additional services provided under EPIC that may be over and above interventions provided by Ohio START and treatment as usual (TAU). In the first stage, two comparison counties will be identified for each of the two intervention counties. One comparison county will be part of the Ohio START program while the second will be a county that has no major interventions to address substance use among child welfare families. Counties are matched based on child population size, rate of child protective services referrals, percent of naloxone administrations per adult population, percent white, percent poverty, child welfare tax levy, and to the extent possible, behavioral health service availability. During the second stage, EPIC families (*N* = 250) are matched with substance using families in Ohio START (*N =* 250) and those receiving treatment as usual (*N =* 250).

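### Outcomes the abstract calls primary have only a within-group test stated, although the design claims to isolate EPIC's effect over Ohio START and usual treatment

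*Protocol article*

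**What the plan says.** The abstract states: "Primary outcomes including addiction severity, child trauma symptoms, resilience, and attachment are assessed at baseline and at program completion". It is the only place in the article that labels outcomes as primary. The measures for all four are described under Parent and child well-being outcomes.

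The Evaluation design section says the design can assess "the independent effects of additional services provided under EPIC that may be over and above interventions provided by Ohio START and treatment as usual". To that end, "EPIC families (*N* = 250) are matched with substance using families in Ohio START (*N =* 250) and those receiving treatment as usual", giving 750 in total.

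The Statistical plan then treats the outcome types differently:

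- **Length of stay in care:** "survival analysis will be utilized to assess program effects on length of stay in out of home care".
- **Reunification, later investigations and substantiations:** logistic regression.
- **Well-being outcomes, with the ASI as an example:** "a paired samples t-test will be conducted to examine the changes in mean scores in child, parent and caregiver well-being outcomes", from baseline to 6 months.
- **Outcome measures generally:** "A series of linear regressions will be used to estimate the relationship between our outcome measures and various independent variables (e.g., age, biological sex").

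The Power analysis section gives N = 750 for the survival and logistic models and N = 250 for the paired t-tests (power 0.88) and linear regressions (power 0.99), at effect size 0.2 and type I error 0.05.

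On data, the section on sources lists the EPIC family surveys and describes no survey of comparison families. For the comparison groups, the Statistical plan promises baseline description: "Baseline descriptive statistics including sociodemographic characteristics, addiction severity and child welfare allegations will be provided for EPIC participants and comparison groups".

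**The concern.** The question is comparative: does EPIC add anything to Ohio START or to usual treatment? A paired t-test has no comparator. It asks whether the mean changed between two visits, and every cause of change enters the answer. Parents are enrolled shortly after a child welfare investigation and after scoring at or above a threshold on a substance-use screen. Some improvement could follow from the crisis passing, from services any family would receive, or from regression to the mean.

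If the plan is followed as written, any such improvement would be credited to EPIC on the outcomes that the abstract puts first. Matched comparison groups exist, but no stated analysis uses them for these outcomes.

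**Working it through.** **1. Which families does the paired test cover?** Inputs from the Power analysis section: effect size 0.2, N = 250, type I error 0.05 (sidedness not stated). Power comes from the noncentral t distribution with n − 1 degrees of freedom and noncentrality 0.2 × √n.

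| Pairs | Noncentrality | Two-sided power |
|---|---|---|
| 250 | 0.2 × √250 = 3.16 | 0.883 |
| 500 | 0.2 × √500 = 4.47 | 0.994 |
| 750 | 0.2 × √750 = 5.48 | above 0.999 |

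The stated 0.88 reproduces as a two-sided test on 250 pairs (one-sided gives 0.934). That is the size of one group. The survey source is named for EPIC families, so the group is probably EPIC.

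**2. Do the regressions supply a comparison?** They are also powered at N = 250, and the article names no group term for them. With the 0.2 read as f², power at N = 250 is 0.997 with 20 predictors and closer to 1 with fewer. The stated 0.99 is therefore of the right order, but the article gives neither the metric nor the number of predictors, so it cannot be pinned down. The argument does not depend on it.

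**3. What does the paired test do when EPIC has no effect?** Suppose scores improve by δ, in SDs of the change score, for reasons other than EPIC. The chance of a significant result is the power in step 1 with δ in place of 0.2. The values of δ are assumptions.

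| Background change δ | δ × √250 | Chance of significance |
|---|---|---|
| 0.1 | 1.58 | 35% |
| 0.2 | 3.16 | 88% |
| 0.3 | 4.74 | 99.7% |

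**4. What would a controlled comparison deliver?** EPIC against one comparison group, 250 v 250, d = 0.2 in outcome SDs, two-sided 0.05. Unadjusted noncentrality is 0.2 × √(250 × 250 / 500) = 0.2 × √125 = 2.24, giving power 0.61. About 393 per group would be needed for 80%. Adjusting for baseline replaces d by d / √(1 − r²), where r is the correlation of baseline with follow-up (assumed; none is given).

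| r | Adjusted d | Power |
|---|---|---|
| 0.3 | 0.210 | 0.65 |
| 0.5 | 0.231 | 0.73 |
| 0.6 | 0.250 | 0.80 |
| 0.7 | 0.280 | 0.88 |

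None of these allows for clustering by county or for attrition. The paired test's 0.2 is in SDs of change and this one is in outcome SDs. The two units coincide only at r = 0.5, where √(2(1 − r)) = 1.

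**The case against.** The best defence is that the authors never meant a controlled analysis here. Objectives 2.1 to 2.3, on placement, reunification and recidivism, name a comparator. Objectives 3.1 to 3.3, on addiction severity, trauma, resilience and attachment, do not. The sentence about independent effects describes the design as a whole and singles out no well-being outcome. On this view the controlled question belongs to the administrative outcomes in 750 families, and the fault is the abstract's label. That may explain the choice, but it leaves the abstract and the Evaluation design section at odds with the analysis. Nor is this silence left to an analysis plan: the article fixes a test, a sample size and a power for these outcomes.

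Four stronger readings are tempting but unsupported.

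- **The test is certainly EPIC-only.** The Statistical plan does not say so. It is an inference from N = 250 and the named survey source, and the detailed power report in Additional file 1 is not shown. A paired test lacks a between-group contrast whichever families are in it.
- **The regressions exclude program group.** Age and sex are given as examples, so the list is open. One can say only that no group term is named and that N is one group's size.
- **A false positive is close to certain through regression to the mean.** Entry is by the UNCOPE, while addiction severity is measured by the ASI-SR. The article gives no correlation between them and describes no selection on child trauma, resilience or attachment. The size of any spurious change is unknown.
- **The data for a controlled comparison are already planned.** Comparison groups are promised baseline addiction severity only. Trauma screens are also recorded in the Needs Portal, but that is described as the EPIC partners' system. No follow-up of comparison families on these measures is described.

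**Conclusion.** The concern stands in a limited form. For the four outcomes called primary in the abstract, the article states no contrast between EPIC and either comparison group. As written, the analysis can show that scores changed, but not that EPIC changed them. The exposure depends on background change: 35% to 99.7% chance of a significant result for an assumed 0.1 to 0.3 SD of change with no program effect.

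It does not follow that the whole study lacks a controlled analysis. Length of stay, reunification and later child welfare involvement have models sized at all 750 families and are outside this point.

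**What to change.** First state whether Ohio START and usual-treatment families complete the same measures at baseline and follow-up, and from which source.

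- **If they do:** analyse each of these outcomes by a baseline-adjusted between-group model. Regress the follow-up score on group (EPIC v Ohio START, EPIC v usual treatment), baseline score and matching factors. Keep the paired t-test as description. Replace the power of 0.88 with a figure for this contrast, stating the assumed baseline correlation and allowing for clustering and attrition.
- **If they do not:** relabel these outcomes, in the abstract as well, as uncontrolled within-group descriptions. Make no claim from them about effectiveness over Ohio START or usual treatment, and rest the controlled claim on the SACWIS outcomes in all 750 families.

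The first route costs stated power: 0.61 unadjusted at d = 0.2, or 0.73 and 0.88 at assumed correlations of 0.5 and 0.7, all before clustering and attrition. It could also require follow-up data collection that the article does not describe. The second needs only changes of wording but narrows what the study can claim.
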